### Specific Objectives

The first objective of the study is to examine the effect of 3MDR therapy on combat-related TR-PTSD and moral injury symptoms, behaviors, and physiological measures for CAF-SMs and veterans who have not benefited from other trauma therapies. The second objective is to examine the perceived technological acceptance and usability of 3MDR by CAF-SMs and veterans with combat-related TR-PTSD as well as 3MDR clinicians and operators. The third objective is to examine the effects of 3MDR on the operators and clinicians who provide this intervention to military members and veterans with combat-related TR-PTSD. In addition to conventional statistical analyses, the final objective of this study is to explore the application of machine learning in an attempt to identify individual data patterns that may predict diagnosis, severity, and potential treatment outcomes.

### Hypotheses

Related to the objectives above, we have derived the following four hypotheses for this study.

Hypothesis 1: Participants’ symptoms of combat-related TR-PTSD will decrease during the 3DMR therapy compared with treatment as usual.

Hypothesis 2: CAF-SMs, veterans, 3MDR clinicians, and operators will perceive 3MDR to be a novel intervention with adequate perceived technology acceptance and usability.

Hypothesis 3: 3MDR operators and clinicians will not experience adverse mental health effects, including secondary trauma and stress, that affect their daily functioning as a result of 3MDR delivery.

Hypothesis 4: Machine-learning analysis will generate two accurate predictive models that may portend diagnosis, severity, and potential treatment outcomes in CAF-SMs and veterans with combat-related TR-PTSD.

## Methods

### Intervention

The 3MDR intervention takes place in an immersive CAREN, a room-sized, three-dimensional VR system that facilitates full engagement. A treadmill located in a central platform in the CAREN is surrounded by 240° floor-to-ceiling screens with motion-capture technology. In each session, the participant continually walks on the treadmill while briefly listening to self-selected music reminiscent of their military deployment(s) prior to viewing a series of 7 self-selected images related to their traumatic events projected onto the screen. The participant is directed to engage in their selected image and walk toward it. Each 3MDR session follows a repetitive cycle of a preplatform phase (A), which is a mental and physical warm up; a platform phase (B) when the VR environment changes, providing a visual and auditory cue of movement into cycles of active therapy; and, following a mental cool-down period, a postplatform phase (C), during which the participant and clinician reflect on the session, and focus on important or newly arisen cognitive and emotional associations (Figure 2). A self-care plan is also reviewed prior to the participant leaving the CAREN. A typical 3MDR session lasts 90 minutes, including the participant walking on the platform for 45-60 minutes (equivalent to 3-4 km).

**Figure 2 figure2:**
[figure not shown]
Schematic overview of a single multimodular motion-assisted memory desensitization and reconsolidation (3MDR) session. A session consists of a preplatform phase (A), platform phase (B), and postplatform phase (C). Used with permission [25]. VR: virtual reality; SUD: Subjective Units of Distress scale.

In the context of the full-service hospital setting, a risk mitigation strategy will be implemented. Clinicians providing 3MDR who have vast experience with trauma-affected populations, including CAF-SMs and veterans, will be authorized to provide mental health services. Clinicians and operators will continually assess the safety of participants during sessions, and will stop the intervention and implement codes or safety protocols if required. Participants will be debriefed after therapy to determine if they are safe to leave the site and prepared to follow their self-care and safety plan. Alternate participant transportation will be utilized for participants if required.

3MDR Satisfaction	Subjective Interview		1	1	1	1	1	1	1

^a^PTSD: posttraumatic stress disorder.

^b^LEC5: Life Events Checklist for DSM-5.

^c^CAPS5: Clinically Administered PTSD Scale for DSM-5.

^d^PCL-5: PTSD Checklist for DSM-5.

^e^GAD-7: Generalized Anxiety Disorder Scale, 7-item.

^f^PHQ-9: Patient Health Questionnaire, 9-item.

^g^PABQ: Posttraumatic Avoidance Behavior Questionnaire.

^h^PDEQ: Dissociative Experiences Questionnaire.

^i^AUDIT: Alcohol Use Disorder Identification Test.

^j^MISS-M: Moral Injury Symptom Scale for Military.

^k^DERS-18: Difficulties in Emotional Regulation Scale.

^l^CD RISC-25: Connor-Davidson Resilience Scale.

^m^OQ-45: Outcome Questionnaire 45.

^n^EQ-5D: EuroQol-5D-5L.

^o^EQVAS: EuroQol-Visual Analog Scale.

^p^UTAUT: Unified Theory of Acceptance and Usability of Technology.

^q^SUDS: Subjective Units of Distress Scale.

^r^CSQ-8: Client Satisfaction Questionnaire.

^s^3MDR: multimodular motion-assisted memory desensitization and reconsolidation.

^t^3MDR-Q: multimodular motion-assisted memory desensitization and reconsolidation questionnaire.

### Recruitment

Regular and reserve CAF-SMs and veterans will be recruited through established relationships with the CAF, Operational Stress Injury Clinics, the Royal Canadian Legion Alberta/Northwest Territories Command, and local community service providers supporting CAF-SMs and veterans. Participants will also be recruited through word of mouth among potential participants. Eligible participants include English-speaking regular and reserve CAF-SMs and veterans aged 18-60 years who meet the Diagnostic and Statistical Manual-5 (DSM-5) criteria for a diagnosis of PTSD. This includes: (1) symptoms lasting more than 3 months; (2) a score of 30 or higher on the DSM-5 Clinician-Administered PTSD Scale, Fifth Edition (CAPS-5) interview; (3) trauma related to combat experiences; and (4) have had a nonresponse to at least two types of evidence-based PTSD treatments where at least one of these treatments was a psychotherapeutic intervention. It is permitted that the second treatment is a pharmacological intervention. Participants must also be stable on their psychotropic medication for a period of 4 weeks before entering the trial and agree to notify researchers of medication adjustments during the course of the trial. Participants with comorbidities will be included if they satisfy the other criteria and PTSD is considered the primary diagnosis. Participants must also have the cognitive capacity to provide informed consent. Participants will be excluded from the study if they demonstrate signs of acute suicidality, psychosis, or reduced cognitive processing that would exclude them from following directions or providing informed consent. Participants will also be excluded if it is determined that they are unable to walk at a normal pace for 30-45 minutes on a treadmill, or if their physical size or abilities are not compatible with the CAREN system. For CAF-SMs and veterans, screening by a research team member will consist of an interview to discuss their previous military employment/deployments, current and past medical history, history and experiences of previous PTSD interventions, and overall suitability for the study.

Recruitment of 3MDR clinicians and operators (N=12) will be conducted through word of mouth among the six international 3MDR research teams located in the Netherlands, the United States (California and Maryland), the United Kingdom (Wales), and Canada (Alberta and Ontario). Clinicians and operators who have received training for 3MDR and completed 6 weeks of interventions will be eligible for a pre/post evaluation. Voluntary written informed consent will be obtained from all participants.

The control group will undergo screening for eligibility and baseline assessment, followed by 9 weeks of treatment as usual while the intervention group receives the 3MDR intervention. They will then be provided an opportunity to cross over into the intervention group.

For the introductory session, intervention group participants will become accustomed to the CAREN system by practicing the process associated with 3MDR, including walking on the treadmill while looking at a neutral image as the clinician guides them through the 3MDR protocol. The participant will be asked to provide (1) images reminiscent of the traumatic deployment event that preceded a PTSD diagnosis, ranked according to the emotional distress that each elicits (ie, from least to greatest level of distress); and (2) digital music tracks of a song that reminds them of their deployment and other sounds or music that provide positive feelings. A secondary purpose of this introductory session is also to transfer trust from their service provider to the 3MDR researchers and clinicians. One week after the introductory session, the 3MDR therapy will be initiated and participants will undergo 6 90-minute sessions.

### Randomization and Blinding

Participants will be randomized to the 3MDR or treatment as usual groups in a parallel design. A research assistant will utilize computerized random number allocation to assign participants to either the 3MDR or treatment as usual groups and maintain a confidential log of which participants are assigned to the respective groups. In addition, participants will be randomly assigned to the clinician that they will be engaging with for 3MDR. Participants, assessors, 3MDR clinicians, and other health care providers will not be blinded to the group allocation.

### Sample Size

A sample size calculation was conducted using G*Power 3 [55], based on the primary hypothesis that 3MDR would result in significantly lower clinician-rated PTSD symptoms as compared to treatment as usual. To detect a significant interaction with at least a medium effect size, a minimal sample size of 17 participants was determined for each group. Because of an estimated 10% dropout and some attrition at measurements, the sample size was set at 20 participants in each group (Cohen f=1.0) using general linear modeling with one within-subjects factor (2 time points) and one between-subjects factor (2 interventions), and assuming a correlation of r=0.5 between the repeated measures, an α-level of .05, and a power (1 – β) of 0.8.

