### Overall Aims

This protocol describes a novel study to assist with the knowledge translation of the underpinnings of 3MDR as a therapeutic intervention. The primary study aim is to investigate whether the 3MDR intervention reduces symptoms of combat-related TR-PTSD and moral injury compared with treatment as usual among Canadian Armed Forces service members (CAF-SMs) and veterans. The study will be the first of its kind to examine the technology acceptance and usability of the Computer-Assisted Rehabilitation ENvironment (CAREN) VR system for 3MDR by participants, 3MDR clinicians and operators, as well as the impact of delivering 3MDR on clinicians and operators. Further, the longitudinal nature of the study will facilitate analysis of the longevity of possible 3MDR treatment effects for up to 6 months postintervention. This study will also address the possible effect of 3MDR on the constructs of moral injury and resilience. Further, as examination of relationships of psychological and biological factors to effective PTSD treatment has become critically important in attempts to understand the pathogenesis of TR-PTSD and to identify novel therapeutic targets [48-50], biomarker measurements and machine learning will be employed. Classifying neuropsychiatric disorders on the basis of objective and practical biomarkers aims to inform the diagnosis and selection of therapeutic approaches [51-54]. Machine-learning analysis will attempt to develop predictive models that can be used for individual diagnosis and prediction of the course of illness and effectiveness of treatment. Biomarker and machine learning utilization is a unique and novel addition to the study of 3MDR that has yet to be incorporated into other 3MDR studies internationally.

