### Data Analysis

#### Objective 1: Effectiveness of 3MDR

The quantitative analysis strategy for this study will include a variety of descriptive, parametric, nonparametric, univariate, and multivariate approaches, as well as machine-learning techniques.

Descriptive statistics will be used to summarize demographic data of participants, including mean values, frequencies, and proportions.

Baseline between-group differences in sociodemographic, clinical, and neuropsychological variables will be assessed. For psychological outcomes, including self-reported PTSD symptom severity, anxiety and depression symptoms, and avoidance behavior, analyses will be conducted using mixed linear models. All of the analyses above will be carried out on an intent-to-treat basis. A two-tailed *P*<.05 will be considered statistically significant.

For preliminary assessment of the relation between treatment outcomes and relevant predicting

variables, exploratory regression analyses will be performed and a predicting variable will be considered to have potential predicting value in cases of *P*<.20. Predictors will then be combined in a regression model to determine which variables most strongly predict 3MDR treatment success. Missing data points, potentially due to missed visits or outcome measure abnormalities, will be handled with the last observation carried forward analysis of covariance [59].

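### The trial is sized on clinician-rated PTSD alone, but the primary aim adds moral injury and the analysis section never names the clinician-rated scale

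*Protocol article*

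**What the plan says.** All references are to the protocol article.

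- **Sample Size.** The calculation is "based on the primary hypothesis that 3MDR would result in significantly lower clinician-rated PTSD symptoms as compared to treatment as usual", at "an α-level of .05, and a power (1 – β) of 0.8". CAPS-5 is the only clinician-administered PTSD severity scale in Table 1.
- **Overall Aims.** "The primary study aim is to investigate whether the 3MDR intervention reduces symptoms of combat-related TR-PTSD and moral injury compared with treatment as usual".
- **Hypotheses.** Hypothesis 1 reads "Participants’ symptoms of combat-related TR-PTSD will decrease during the 3DMR therapy compared with treatment as usual". It names no scale and no fixed time point, and it leaves out moral injury.
- **Specific Objectives.** The first objective is "to examine the effect of 3MDR therapy on combat-related TR-PTSD and moral injury symptoms, behaviors, and physiological measures".
- **Data Analysis, Objective 1.** "For psychological outcomes, including self-reported PTSD symptom severity, anxiety and depression symptoms, and avoidance behavior, analyses will be conducted using mixed linear models". The threshold is then "A two-tailed *P*<.05 will be considered statistically significant". Neither CAPS-5 nor a clinician rating is mentioned in this section.
- **Table 1.** CAPS-5 is listed for both groups at Week 1 and Week 9. PCL-5 and MISS-M are listed for the control group only from Week 9. No measure is marked as primary.

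**The concern.** A reader who asks which single test decides the trial gets different answers. The sample size points to the clinician rating of PTSD. The primary aim points to PTSD and moral injury. The analysis section names the self-report of PTSD and applies the same significance threshold to everything.

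Two things are at stake. First, a significant result on PCL-5 or MISS-M could be presented as meeting the primary aim although the trial was sized on CAPS-5. Participants and assessors are unblinded (Randomization and Blinding), so the choice of scale also decides whose unblinded rating carries the conclusion. Second, a two-part primary aim needs its own error control and its own power, and the sample size provides for one outcome.

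The question is live. The Results section reports 11 participants who have completed the intervention, and Triangulation of Data plans an integration of results after roughly every 5 participants. A choice of scale left open now could be made with data in view.

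**Working it through.** **1. Reproduce the stated sample size.** Inputs from Sample Size: 2 groups, m = 2 time points, correlation r = 0.5, alpha .05, power 0.8, medium interaction effect (f = 0.25 is assumed as the G*Power convention). For the within-between interaction:

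- noncentrality λ = f² × N × m / (1 − r), with 1 and N − 2 degrees of freedom
- N = 34: λ = 0.0625 × 34 × 2 / 0.5 = 8.5 on 1 and 32 df, power 0.807
- N = 32: λ = 8.0, power 0.78

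So 34 in total, or 17 per group, is the smallest equal allocation that reaches 0.8. The stated figure reproduces, for one outcome tested at the whole .05. (The printed f = 1.0 would give N = 6, so 17 did not come from it. That is a separate matter.) With 10% dropout from 40, 36 are evaluable: λ = 9.0, power 0.83.

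**2. What the two-part aim would need.** Same formula, with alpha divided equally:

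| Primary scales | Alpha each | Evaluable N for power 0.8 | Power per scale at 36 |
|---|---|---|---|
| CAPS-5 | .05 | 34 | 0.83 |
| CAPS-5, MISS-M | .025 | 42 | 0.74 |
| CAPS-5, MISS-M, PCL-5 | .0167 | 46 | 0.68 |

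With two primaries, even all 40 enrolled participants would fall just short: λ = 0.0625 × 40 × 2 / 0.5 = 10.0, power 0.79 at alpha .025.

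**3. Error rate if the alpha is not divided.** Each scale is tested two-sided at .05 and the null is true for all. Under independence the chance of at least one false positive is 1 − 0.95^k. For correlated tests it was simulated with equicorrelated normal statistics. The correlations are assumptions; the article gives none.

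| Assumed correlation | 2 scales (PTSD, moral injury) | 3 scales (CAPS-5, PCL-5, MISS-M) |
|---|---|---|
| 0 | 9.8% | 14.3% |
| 0.3 | 9.5% | 13.6% |
| 0.5 | 9.1% | 12.6% |
| 0.7 | 8.3% | 10.9% |
| 0.8 | 7.9% | 9.8% |

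These count errors in both directions. Only a result in favour of 3MDR could be reported as meeting the aim, and that is about half of each figure. Under independence it is 1 − 0.975² = 4.9% for two scales and 1 − 0.975³ = 7.3% for three, against 2.5% for a single test.

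**4. Which scale fits the powered test.** The powered test is a group-by-time interaction over two time points, so it needs a baseline and a post value in both groups. As Table 1 stands, CAPS-5 is the only PTSD severity scale that has both. Study Timeline and Data Collection, however, says that data come from both groups at T0 and T1 and that the clinical measures are taken at every time point. The table and that section disagree and must be reconciled.

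**The case against.** The strongest reply is that the article does single out one outcome. Sample Size states a primary hypothesis with a rater, a comparator, a design and an alpha, and Hypothesis 1 agrees with it on the construct. The analysis sentence introduces its list with the word including, so CAPS-5 is unnamed rather than excluded. The first objective is an objective, and one that spans several domains does not contradict a single primary hypothesis. The outcome hierarchy and the multiplicity rules may also stand in the full protocol or analysis plan, which are not shown.

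Most of this stands, and it limits the point. A reader might infer that the .05 test could attach to any of the dozen clinical scales that Table 1 assesses in both groups at Week 9, with a 46% chance of a false positive (1 − 0.95^12). The documents do not support that. The primary aim covers only PTSD and moral injury, so a result on alcohol use or quality of life could not meet it. The 46% also assumes independent scales and counts both directions; in favour of 3MDR alone it is 1 − 0.975^12 = 26%. It is an outer bound only. Nor can one say that the plan excludes CAPS-5 from analysis.

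The reply does not remove the conflict between passages that are printed. The primary aim includes moral injury, while the primary hypothesis and Hypothesis 1 do not. The section that states the model and threshold names the self-report version of PTSD and omits the rating on which the trial was sized. That is a mismatch in what the article states, not detail left to another document.

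**Conclusion.** The point holds in this limited form: the primary aim, the powered hypothesis and the named analysis do not agree, and CAPS-5, PCL-5 and MISS-M are the realistic candidates for the primary test. With undivided alpha, the two-sided error rate is about 8%-10% for PTSD plus moral injury and about 10%-14% for all three scales, of which about half would favour 3MDR. This rests on assumed correlations of 0.3-0.8. The sample size is sound for one outcome at f = 0.25. It does not support two primaries at .025 each, which need about 42 evaluable participants and have power of about 0.74 per scale at 36.

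The plan should be corrected, but the design survives: the sponsor's own power basis already identifies a workable primary outcome.

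**What to change.** Issue a dated amendment before any further between-group look at the data. It should:

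1. State one primary outcome consistent with Sample Size: CAPS-5 total severity, baseline to Week 9, 3MDR versus treatment as usual, two-sided .05.
2. Name CAPS-5 and its model in the Data Analysis section. Adjustment for baseline CAPS-5 is preferable. It replaces the interaction test used for sizing, and the amendment should say so. It should not cost power: at r = 0.5 the variance factor is 1 − r² = 0.75, against 2(1 − r) = 1.0 for change scores.
3. Label MISS-M, PCL-5 and the other scales as secondary in Overall Aims and Data Analysis.
4. Reconcile Table 1 with Study Timeline and Data Collection on whether controls have a baseline for PCL-5 and MISS-M, since this determines how those two can be analysed.

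If the sponsor wants moral injury to stay primary, the alternative is to divide the alpha or fix a test order, and to restate the power. How the secondary scales are tested beyond this is a matter of choice.

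The cost is that moral injury moves from the primary aim to a secondary outcome. With 11 participants through the intervention, this is also a mid-trial change whose date and reason must be documented. No extra participants are needed for the single-primary version.

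### The sample size paragraph contradicts itself: Cohen f=1.0 is not a medium effect and cannot yield 17 per group, a number that corresponds to a 1.0 SD difference in change

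*Protocol article*

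**What the plan says.** The Sample Size section of the protocol article ties the calculation to the between-group hypothesis that "3MDR would result in significantly lower clinician-rated PTSD symptoms as compared to treatment as usual" and names G*Power 3 as the software. It then says: "To detect a significant interaction with at least a medium effect size, a minimal sample size of 17 participants was determined for each group". Allowing for 10% dropout and some further attrition, it continues: "the sample size was set at 20 participants in each group (Cohen f=1.0) using general linear modeling". The remaining inputs are also printed: a model with two time points and two interventions, "assuming a correlation of r=0.5 between the repeated measures", an alpha of .05 and power of 0.8. The Data Analysis section sets a two-tailed 5% level.

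The section does not say which G*Power effect-size option was used. It also does not translate the effect into SD units or points on the clinician-rated scale, which in Table 1 is the CAPS-5.

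**The concern.** The paragraph describes its target effect in two ways. Medium, on the usual f scale, is 0.25. The printed number is 1.0, four times that and far above the conventional value for large (0.40). Because every other input is given, the calculation can be repeated, and only one of the two descriptions can be compatible with 17 per group.

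The effect size is the figure on which the sample size rests, and a reader needs it to judge what the trial can detect. The abstract's conclusions say that the results will inform a full-scale trial. The article does not say that this planning value would be carried forward, but anyone who did reuse f=1.0 would start from a number that gives a trial of about six people.

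**Working it through.** **Inputs, all from the Sample Size section:** k=2 groups, m=2 time points, r=0.5, alpha=.05, power=.80, stated result 17 per group (N=34). The test is the group-by-time interaction, F with 1 and N−2 degrees of freedom. This is equivalent to a two-sided two-sample t test on change scores.

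**1. Reproduce the stated 17 per group.** Under G*Power's default parameterisation the noncentrality is λ = f²·N·m/(1−r).
- f=0.25, N=32: λ = 0.0625 × 32 × 2/0.5 = 8.0, power 0.781.
- f=0.25, N=34: λ = 0.0625 × 34 × 2/0.5 = 8.5, power 0.807.

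So f=0.25 needs 34 in total with equal groups, which is exactly 17 per group.

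**2. Put in the printed f=1.0.** For N=6, λ = 1 × 6 × 2/0.5 = 24 and power is 0.948. At N=34 power is essentially 1. The printed value therefore leads to 3 per group.

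**3. Try other definitions of f.**

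| Definition | λ | N needed at f=1.0 | f that gives N=34 |
|---|---|---|---|
| G*Power default, interaction | f²·N·m/(1−r) | 6 (power 0.948) | 0.25 (power 0.807) |
| Cohen-style | f²·N | 12 (power 0.876) | 0.5 (power 0.807) |
| SPSS-style | f²·(N−2) | 12 (power 0.813) | not 0.5, which needs 36 (power 0.809) |
| Between-factors test (not the interaction) | f²·N·m/(1+r) | 10 (power 0.891) | not 0.25, which needs 98 (power 0.808) |

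No definition brings f=1.0 near 34. Two of the values tried reproduce 34 exactly: f=0.25 (default) and f=0.5 (Cohen-style).

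**4. Convert to a scale that does not depend on the definition.** In a 2×2 interaction under the default option, each cell departs from additivity by f·SD, so the difference in change between groups is D = 4·f·SD. The SD of a change score is SD·√(2(1−r)) = SD·√1 = SD at r=0.5.
- f=0.25 (default): D = 4 × 0.25 = 1.0 SD.
- f=0.5 (Cohen-style): λ = 0.25·N. For a standardised difference d in change, λ = d²·N/4, so d = 2 × 0.5 = 1.0. The effect is the same.
- f=1.0 (default): D = 4.0 SD. Under Cohen-style f it would be d = 2 × 1.0 = 2.0.

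Check: a two-sample t test with d=1.0 and 17 per group has noncentrality √(17/2), whose square is 8.5 as in step 1, and power 0.807. A simulation of 20,000 trials with a 1.0 SD difference in change and r=0.5 gave 0.809.

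**5. Power of the planned design on the change scale.**

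| Difference in change | 17 per group | 18 per group | 20 per group |
|---|---|---|---|
| 1.0 SD | 0.807 | 0.830 | 0.869 |
| 0.5 SD | 0.293 | 0.308 | 0.338 |

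**6. Dropout.** 17/(1−0.10) = 18.9, rounded up to 19. Twenty per group is consistent with 10% dropout plus some further attrition. With exactly 10% dropout, 18 per group remain.

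**The case against.** The strongest objection is that nothing about the trial's size is wrong. The protocol promises power for a medium interaction. On the conventional f scale in G*Power that means f=0.25, and this is delivered: 0.807 at 17 per group and 0.869 at 20. On this view f=1.0 is a reporting slip beside a correct number. This stands as far as the number of participants is concerned. It does not rescue the printed f, which is wrong under every definition tried.

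Three stronger readings are tempting, and the documents do not support them.

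- *The trial fails to deliver its promised 80% power for a medium effect.* A reader might infer this from the power of 0.29 to 0.34 at 0.5 SD. The protocol never sets 0.5 SD as its target. That benchmark comes from the convention for two-group mean differences, and the document states its target as an interaction. The low figures show what medium does not mean here; they do not show a broken promise.
- *Only f=0.25 can produce 17 per group.* The option used is not named, and f=0.5 under the Cohen-style option gives the same 34 and the same power. The default is the likelier reading because it agrees with the word medium, but the article does not establish it.
- *The printed f=1.0 is really d=1.0 with the wrong label.* The coincidence with the 1.0 SD in step 4 makes this plausible, but no statement in the article confirms it.

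**Conclusion.** The paragraph is internally inconsistent, and the effect size behind the sample size is wrong as written. Cohen f=1.0 requires 6 participants in total (12 under Cohen-style f), not 34, and it is not a medium effect. Seventeen per group corresponds to a between-group difference in change of 1.0 SD, under either definition of f that reproduces it.

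This rests on the printed inputs, in particular r=0.5 and equal groups, and on the interaction test that the section describes. The conclusion about f=1.0 does not depend on which G*Power option was used. The identification of f=0.25 does, and remains the most likely value, not an established one.

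The finding does not show that 20 per group is too few for a 1.0 SD difference. It does show that a reader who takes medium to mean half an SD will overestimate the trial's sensitivity: a non-significant result would not exclude a difference of that size.

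**What to change.** Keep N=40. Check the G*Power record and replace Cohen f=1.0 with the value and effect-size option actually used, most likely f=0.25 with the default option for the within-between interaction. Then add:

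- that this equals a between-group difference in CAPS-5 change of 1.0 SD at r=0.5, with power 0.807 at 17 and 0.869 at 20 per group;
- that medium refers to the f-scale convention for the interaction;
- as a clarification, that power for a 0.5 SD difference in change is about 0.29 at 17 and 0.34 at 20 per group, so a non-significant result would not exclude an effect of that size.

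If the record shows other inputs, the SD equivalent and the power figures should be recomputed from them. The change costs wording only: no extra participants and no change to allocation, alpha or analysis. The price is that the stated sensitivity of the trial looks less favourable.

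### The only test tied to the primary CAPS-5 endpoint is a two-time-point interaction without baseline adjustment; name one primary model, with Week 1 CAPS-5 as a covariate

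*Protocol article*

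**What the plan says.** Under Methods, Sample Size, the calculation is "based on the primary hypothesis that 3MDR would result in significantly lower clinician-rated PTSD symptoms as compared to treatment as usual". The aim is "To detect a significant interaction with at least a medium effect size", "using general linear modeling with one within-subjects factor (2 time points) and one between-subjects factor (2 interventions", "assuming a correlation of r=0.5 between the repeated measures", with "an α-level of .05" and power 0.8. The section gives 17 per group, raised to 20 for dropout and attrition, and prints Cohen f=1.0. It names no covariate.

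Under Data Analysis, Objective 1, "Baseline between-group differences in sociodemographic, clinical, and neuropsychological variables will be assessed". For psychological outcomes, with self-reported PTSD severity listed and CAPS-5 not named, "analyses will be conducted using mixed linear models". An analysis of covariance appears once, in the sentence on missing data (last observation carried forward), and its covariate is not stated. Tests are two-tailed at .05.

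Table 1 schedules CAPS-5, the only clinician-rated PTSD severity scale listed, at Week 1 and Week 9 for both groups.

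**The concern.** With two time points and complete data, the interaction F test is the two-sample t test on change from baseline. Baseline is then subtracted with a fixed slope of 1. If the correlation is 0.5 and the SDs are equal, the best slope is 0.5, so the change score over-corrects.

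Two things are at stake in a trial of 40. The first is precision. The second is sensitivity to chance imbalance: Randomization and Blinding describes computerised allocation and mentions no stratification by severity. With a CAPS-5 entry threshold of 30 (Recruitment), regression to the mean is to be expected, and it falls more heavily on the group that happens to start higher.

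The Data Analysis section does not settle the matter. A mixed model with a free baseline mean in each group, fitted to Week 1 and Week 9, gives the change-score contrast on complete data. One with a common baseline mean gives the adjusted contrast. The text does not say which is meant.

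**Working it through.** **Inputs.** From Sample Size: 2 groups, m=2 time points, r=0.5, alpha .05, power 0.8, 17 and then 20 per group. From Data Analysis: two-sided testing. Assumed: f=0.25 as the conventional value for a medium effect, and equal SDs at both visits. The documents give no SDs.

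**Reproducing the plan's 17 per group.** For the within-between interaction, lambda = N·m·f²/(1−r), with 1 and N−2 degrees of freedom.
- f=0.25, N=34: lambda = 34 × 2 × 0.0625 / 0.5 = 8.5, power 0.807.
- f=0.25, N=32: power 0.781. The minimum is therefore 34, or 17 per group, which matches the plan.
- f=1.0 (as printed): at most 6 participants in total are needed, so this value does not reproduce 17 per group.

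In a 2×2 layout f=0.25 is a difference in change of 4 × 0.25 = 1.0 SD.

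**Variance of the group contrast, per-participant term in units of SD².**
- Change score: 2(1−r) = 1.00.
- Baseline-adjusted: 1−r² = 0.75.
- Ratio: (1+r)/2 = 0.75, a 25% cut.

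**Power at r=0.5 and f=0.25.** For the adjusted test, lambda is divided by 0.75 and one degree of freedom is lost. The simulation used 20,000 trials per sample size.

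| Per group | Change score | Adjusted | Gain, formula | Gain, simulation |
|---|---|---|---|---|
| 17 | 0.8070 | 0.9033 | 9.6 points | 8.8 points |
| 18 | 0.8300 | 0.9195 | 9.0 points | 8.3 points |
| 20 | 0.8690 | 0.9447 | 7.6 points | 7.2 points |

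By the formula, the adjusted test reaches 80% power at about 26 participants in total instead of 34.

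**Sensitivity to r (18 per group, f=0.25 held fixed).**
- r=0.3: 0.693 to 0.863, about 17 points.
- r=0.6: 0.903 to 0.953, about 5 points.
- r=0.7: 0.964 to 0.983, about 2 points.

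**Sensitivity to unequal SDs (r=0.5).** Let k be the Week 9 SD divided by the baseline SD. In units of baseline variance, the change-score term is 1+k²−2rk and the adjusted term is k²(1−r²).
- k=1: 1.00 against 0.75, a 25% cut.
- k=1.25: 1.3125 against 1.1719, a 10.7% cut.
- k=1.5: 1.75 against 1.6875, a 3.6% cut.
- k=2: 3 against 3, no cut.

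A ratio below 1 enlarges the gain.

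**Sensitivity to effect size.** With f=1.0 taken literally, power is about 1.00 at 34 participants by either method, so nothing is gained.

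**Chance imbalance.** At 20 per group the baseline difference has an SD of √(2/20) = 0.32 SD. At r=0.5 with equal SDs, half of any imbalance passes into the change-score estimate, favouring the group that starts worse. A typical imbalance therefore moves it by about 0.16 SD. In simulation the slope of the estimate on imbalance was −0.50 unadjusted and 0.00 adjusted.

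**The case against.** The strongest reply is that a sample-size paragraph describes a calculation, not the analysis. Powering on a simple model and analysing with a more efficient one is conservative. Data Analysis names mixed linear models, which could include one with a common baseline mean, and an analysis of covariance, which by definition has a covariate. A condensed article may also leave covariates to an analysis plan that is not shown here.

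Much of this stands. A reader might infer that the trial has committed to an unadjusted change-score test as its primary analysis. The documents do not support that, because Data Analysis leaves the model open. What remains is that Sample Size is the only place linking a test to the clinician-rated endpoint, that test has no covariate, and Data Analysis neither repeats nor supersedes it.

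The size of the gain can also fairly be challenged. The 25% needs equal SDs, and the entry threshold of 30 could restrict the baseline range and make the Week 9 SD the larger one. The power figures need f=0.25, although f=1.0 is printed. Both conditions are carried into the verdict.

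Two further inferences fail. Under randomisation the change-score contrast is unbiased, so the result would not be invalid. And the text says only that baseline differences are to be assessed; it does not say that this assessment selects covariates, so it is not a fault here.

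**Conclusion.** The point holds as one of efficiency and clarity. The only test attached to the primary endpoint is an interaction that, on complete data, ignores baseline as a covariate, and the analysis section does not resolve whether it will be used.

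The 25% variance cut and the gain of about 7 to 10 power points at 17 to 20 per group rest on three conditions: r=0.5 (the plan's own figure), equal SDs, and f=0.25 (the value that reproduces 17 per group). At 18 per group the gain ranges from about 17 points at r=0.3 to 2 at r=0.7. The variance cut is about 11% if the Week 9 SD is 1.25 times the baseline SD.

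The printed f=1.0 conflicts with "at least a medium effect size" and with 17 per group. It is an error in its own right and no ground for dismissing the gain.

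The change should be made because it buys precision and protection against chance imbalance almost for free, not because the unadjusted test would be wrong.

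**What to change.** Reconcile Sample Size with Data Analysis, Objective 1, and state one primary analysis: Week 9 CAPS-5 compared between randomised groups with Week 1 CAPS-5 as a covariate. A mixed model with Week 1 and Week 9 as outcomes and a common baseline mean for both groups is an acceptable alternative. The primary result is then the adjusted group difference at Week 9. Correct or explain f=1.0 in the same edit, and state the difference in SD units that it stands for.

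The cost is a few sentences and one degree of freedom. No visits, measurements or participants are added, since CAPS-5 is already scheduled at both time points in both groups. The trial is unblinded and under way, and Triangulation of Data plans integration of results about every 5 participants, so the model should be fixed and dated before any further look at outcome data.
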